### Study Arms

#### Overview

The participants in both the intervention and usual care groups will receive the standard-of-care rehabilitation in the GEAR program. Those in the intervention group will receive IMT in addition to the GEAR program components, as shown in Table 2.

**Table 2 table2:** Summary of the study procedures.

Study groups	IMT^a^ intervention group with participants with hEDS^b^ or G-HSD^c^ (n=17)	Usual care group with participants with hEDS or G-HSD (n=17)
Standard of care—GEAR^d^ program: baseline (T_0_), 4 weeks from T_0_ (T_1_), 8 weeks from T_0_ (T_2_), and 20 weeks from T_0_ (T_3_)	Aerobic, resistance, neuromuscular stabilization, and balance and proprioception exercises [36]	Aerobic, resistance, neuromuscular stabilization, and balance and proprioception exercises [36]
Baseline assessment (details provided in Table 1)	Baseline assessment: explanation of equipment and tracking IMT device POWERbreathe K5 IMT and exercise logs and Fitbit device and instructions Fitbit device and instructions Exercise logs	Baseline assessment: Fitbit device and instructions Exercise logs
Study intervention: 8 weeks	2 daily IMT sessions of 30 breaths (<5 minutes per session) for 5 days per week, up to 8 weeks IMT starting at 20% of MIP^e^ (up to a maximum of 60%) Intensity progressed by 5% to 10% if the median weekly Borg dyspnea score is <7 Web-based supervision by the study team Weekly check-in with the study coordinator	N/A^f^
Follow-up: week 4 time point	Study assessments will be performed at week 4 from the home environment. Exercise logs and respiratory muscle endurance will be assessed	Study assessments will be performed at week 4 from the home environment. Exercise logs and respiratory muscle endurance will be assessed
End point: week 8 time point	Study assessments conducted at baseline will be performed again at week 8 in the PFT^g^ laboratory. Collection of logs, Fitbits, and IMT device (POWERbreathe K5) will be done at the end of the study	Study assessments conducted at baseline will be performed at week 8 in the PFT laboratory. Collection of logs, Fitbits, and IMT device (POWERbreathe K5) will be done at the end of the study.

^a^IMT: inspiratory muscle training.

^b^hEDS: hypermobile Ehlers-Danlos Syndrome.

^c^G-HSD: generalized hypermobility spectrum disorder.

^d^GEAR: GoodHope Exercise and Rehabilitation Program.

^e^MIP: maximal inspiratory pressure.

^f^N/A: not applicable.

^g^PFT: pulmonary function test.

#### Usual Care Group

The standard-of-care rehabilitation in the GEAR program comprises 8 weeks of aerobic, resistance, neuromuscular stabilization, and balance and proprioception exercises performed in the home environment [1]. The participants in the GEAR program attend in-person or web-based exercise training sessions at the following intervals: T_0_, 4 weeks from T_0_, 8 weeks from T_0_, and 20 weeks from T_0_ to observe maintenance [46]. The GEAR program comprises three major elements: (1) an individualized home-based rehabilitation and exercise therapy, (2) education on the self-management of hEDS or G-HSD symptoms, and (3) a community resource engagement plan. These components are delivered by a team of physiotherapists and kinesiologists.

#### Intervention Group (IMT)

The participants in the intervention group will receive an individual and personalized prescription for an IMT program for 8 weeks. This IMT program will use the POWERbreathe K5 IMT device in the participants’ home environment combined with the standard-of-care rehabilitation as part of the GEAR program, as described earlier. A research coordinator will facilitate these training sessions and monitor the participants via the web for the first 3 sessions in the first week and once a week from weeks 2 to 8. Over 8 weeks, 2 daily IMT sessions of 30 breaths (<5 min/session) will be performed for 5 days per week, starting with 20% of the participants’ T_0_ MIP up to a maximum of 60%. This protocol was developed based on the previous literature on IMT applied in lung transplant candidates at our center [70-72]. The total workload per session (product of inspiratory muscle force and inhaled volume expressed in Joules) will be abstracted from the IMT device. Additional variables abstracted from the device will include inspiratory muscle load (cm H_2_O), mean power per breath (W), and mean volume per breath (Liters).

The participants will be asked to record their resting and post-IMT Borg dyspnea scores for 5 days of the week (2 sessions per day), along with any side effects for each session. The median Borg dyspnea score for the previous week will be reviewed by the research coordinator, and IMT intensity will be increased by 5% to 10% of the T_0_ MIP if the median weekly Borg dyspnea score is <7 (very severe breathlessness with IMT) [54].

The participants will be asked to maintain IMT diaries to assess adherence. They will receive instructions and feedback on how to optimize their home training efforts based on direct observation of their IMT with the POWERbreathe K5 device and review of IMT workload from the device. They will have the possibility to schedule additional sessions with the study team during the week, if further support is needed.

### Trial Outcomes

#### Estimates of Intervention Feasibility

Study feasibility will be assessed through recruitment rate, attrition, IMT program adherence, safety, and satisfaction (Textbox 1).

Feasibility estimates.RecruitmentWe will evaluate the recruitment rate as the number of participants who consented and enrolled relative to the total number of eligible patients approached for eligibility assessment by the research coordinator. The reasons for nonparticipation in the study will be documented. A successful recruitment rate will be defined as 20% in this study.RetentionRetention will be evaluated through participant attrition throughout the intervention period. For each arm of the study, the retention rate will be assessed by measuring the number of participants who completed all assessments compared with the number of participants who enrolled and randomized. A successful retention rate will be defined as ≥80% in this study.AdherenceAdherence to inspiratory muscle training (IMT) in the intervention group will be tracked electronically and through participant logs (number of completed sessions of 30 breaths out of 10 planned sessions per week) with the IMT device over the 8-week period. Adherence will also be assessed during weekly communications with participants as well as through completed daily IMT logs, which will capture IMT training days and IMT prescription (percentage of maximal inspiratory pressure). These data will also be verified after the IMT device is returned. The number of completed IMT sessions will be reviewed from the recordings on the device.The physical activity and exercise behaviors prescribed through the GoodHope Exercise and Rehabilitation Program will be monitored in both the intervention and usual care groups. Daily step counts will be assessed from the Fitbit device. The participants with hypermobile Ehlers-Danlos Syndrome or generalized hypermobility spectrum disorder will be asked to download the Fitbit app on their smartphones or tablets. A 1-page document highlighting the key steps for setting up the Fitbit tracker will be provided. We will also work with the participants via the web to set up the device if any problems arise. The exercise behaviors of the study participants in both groups will be reviewed using the self-reported exercise logs, which capture the exercise type, frequency, intensity, and duration on a daily basis. At the end of the baseline assessment, the study participants in both the usual care and intervention groups will be provided with documents explaining the maintenance and use of the study devices (eg, Fitbit, respiratory muscle endurance trainer, and IMT device for the intervention group).SafetyThe participants will log any adverse effects during the IMT program, which will be reviewed weekly by the research coordinator. Adverse effects are rare; however, symptoms previously observed during IMT include mild chest discomfort, worsening respiratory symptoms (eg, dyspnea), and possibly nausea related to hyperventilation [73]. The participants will also be strongly encouraged to immediately contact a member of the research team if they notice any adverse events. Study personnel will also inquire about chest discomfort or delayed-onset muscle soreness during IMT in weekly meetings to adjust IMT prescriptions and ensure tolerability of training intensity.SatisfactionParticipation satisfaction and motivation to engage with the IMT program will be assessed in the intervention group using a standardized questionnaire administered at weeks 1, 4, and 8 after study enrollment.

#### Primary Pilot Outcome

The primary pilot outcome will be the change in MIP over the 8-week study period to demonstrate the efficacy of IMT, which has been shown to be an important physiological measure in several IMT studies [11,26,35,73].

#### Secondary Outcomes

The secondary outcome measures evaluated will include dyspnea, respiratory muscle structure and function, mood, and HRQL assessed at T_0_ and 8 weeks, as shown in Table 3.

**Table 3 table3:** Study outcomes.

Outcome				Assessment measurement		Time point
**Primary outcome**						
	Respiratory muscle strength		MIP^a^ (cm H_2_O)		Baseline (T_0_) and 8 weeks (T_2_)	
**Secondary outcomes**						
	**Pulmonary function**					
		Spirometry and lung volumes	FEV1^b^ (L), FVC^c^ (L), TLC^d^ (L), RV/TLC^e^ (%)		Baseline (T_0_) and 8 weeks (T_2_)	
		Oscillometry	Oscillometry: respiratory impedance, reactance, and resistance		Baseline (T_0_) and 8 weeks (T_2_)	
		Respiratory muscle endurance time	Time (seconds) using the Philips Threshold trainer at 30% of baseline MIP		Baseline (T_0_), 4 weeks (T_1_), and 8 weeks (T_2_)	
		Diaphragm structure and function	Diaphragm thickness and thickening fraction		Baseline (T_0_) and 8 weeks (T_2_)	

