### Healthy Controls

Healthy adults (aged ≥18 years) will be age- and sex-matched with the participants with EDS and G-HSD. Individuals will be excluded from the study if they meet the following criteria:

Diagnosis of a respiratory, cardiovascular, or musculoskeletal condition that may contribute to exercise limitationPresence of cardiac pacemaker or implantable defibrillatorInsufficient English fluency to provide informed consent or inability to follow study protocolsSelf-reported pregnancyActive smoker (cigarettes or marijuana)

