### Respiratory Parameters

#### Assessment Using PFTs

##### Spirometry and Lung Volumes

Forced expiratory volume in 1 second, forced vital capacity, total lung capacity, and lung volumes (tidal volume, inspiratory capacity, expiratory reserve, and residual volumes) will be evaluated in accordance with the American Thoracic Society guidelines before CPET [40].

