#### Assessment Using CPET

##### Overview

Symptom-limited CPET will be performed on a cycle ergometer (Elema), with exhaled gas measurements captured breath by breath, as routinely applied in our PFT laboratory. Testing will start with 2 minutes of complete rest on the bike, followed by unloaded pedaling for 2 minutes, and then exercise intensity will be increased by 10 to 20 W per minute using a ramp protocol. Blood pressure, 12-lead electrocardiogram, and peripheral oxygen saturation will be continuously monitored. Inspiratory capacity, tidal volumes, and respiratory rate will be measured throughout the exercise to assess for any dynamic hyperinflation and ventilatory reserve. Heart rate (HR) response, peak aerobic capacity, oxygen pulse (measure of cardiac stroke volume), and minute ventilation (product of tidal volume and respiratory rate) will be collected throughout the exercise and up to 2 minutes after test completion with unloaded pedaling, with percent predicted values reported. HR recovery (difference between peak HR and HR 1 minute after exercise) and the chronotropic response index ([peak HR – resting HR × 100] / [220 – age] – [resting HR]) will be collected as a measure of autonomic function [51-53]. Chronotropic incompetence is the inability to decrease HR after exercise or the inability to reach 80% of the maximal age-predicted HR because of abnormal sympathetic activation [51]. Symptom intensity for breathing and leg discomfort with exercise will be measured at rest and every 3 minutes throughout the exercise using the Borg dyspnea [54] and leg fatigue scales [55]. The reasons for exercise cessation will be ascertained from the participants (ie, dyspnea, leg fatigue, both, or other). To ensure participant safety before CPET, 12-lead electrocardiograms will be performed for both the participants with hEDS or G-HSD and healthy controls.

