### Anthropometric Measures

Standard anthropometric measures will be captured for all the participants. Height, weight, waist circumference, and BMI information will be collected for the participants with hEDS or G-HSD from the electronic patient charts. The same measures will be collected for healthy controls during the T_0_ assessments.

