### Statistical Analysis

#### Proposed Data Analyses

For objective 1, we aim to compare respiratory muscle structure and function and PROMs between patients with hEDS or G-HSD and healthy controls and to evaluate the main correlates with dyspnea in patients with hEDS or G-HSD. Descriptive statistics will be used for continuous variables (mean and SD or median and IQR), and frequencies will be used for categorical variables. We will use multivariable regression analysis to compare any differences between groups across respiratory parameters and PROMs, adjusted for EDS subtype (hEDS or G-HSD). We will explore the associations with peak Borg dyspnea scores during CPET using multivariable regression, with possible determinants being MIP, diaphragm thickening fraction, PFC activity, and PFT parameters.

For objective 2, we aim to assess the feasibility of IMT and standard-of-care rehabilitation for improving respiratory muscle strength, exercise capacity, and PROMs compared with standard-of-care rehabilitation alone in patients with hEDS or G-HSD. Descriptive statistics will be used to summarize program adherence, recruitment, participant satisfaction, attrition, and safety in the hEDS or G-HSD study groups. Estimates of within- and between-group differences at T_0_, 4 weeks, and 8 weeks will be reported using means and 95% CI. Paired *t* tests and *t* tests will be used to compare the changes in the primary pilot outcome (MIP) and secondary measures over the 8-week study period within and between the 2 randomized groups.

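### Lung volumes are listed only in litres, and the patient–control comparison neither matches on height nor adjusts for it, which costs precision in a secondary comparison

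*Protocol article*

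**What the plan says.** - **Scale.** Table 3 (Secondary Outcomes) lists "FEV1^b^ (L), FVC^c^ (L), TLC^d^ (L), RV/TLC^e", measured at baseline and 8 weeks. The Spirometry and Lung Volumes section says only that the tests "will be evaluated in accordance with the American Thoracic Society guidelines before CPET" and gives no unit. The one mention of predicted values, "with percent predicted values reported", is in the CPET overview and concerns exercise variables.
- **Who is compared.** Table 1 gives healthy controls the same spirometry and lung volume tests at baseline. The abstract includes pulmonary function among the measures done once in controls for comparison.
- **Matching.** Controls "will be age- and sex-matched with the participants with EDS and G-HSD". Height is not named.
- **Model.** For objective 1, Proposed Data Analyses uses multivariable regression to "compare any differences between groups across respiratory parameters and PROMs, adjusted for EDS subtype (hEDS or G-HSD"). No other covariate is named.
- **Height data.** Under Anthropometric Measures, height and the other body measures "will be collected for the participants with hEDS or G-HSD from the electronic patient charts"; in controls they are collected at the baseline assessment.

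**The concern.** Lung volume in litres rises with body height. When each adult is compared with himself or herself 8 weeks later, height cancels. When 34 patients are compared with 17 other people, it does not. Matching on age and sex removes only the part of height that goes with age and sex, and the one named covariate, EDS subtype, says nothing about body size.

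Two things are at stake. Height adds variance to each litre-scale comparison, so the confidence interval is wider than it need be. And if patients and controls differ systematically in height, that difference would be read as a difference in lung function. The article's background discusses a restrictive pattern and lower vital capacity as possible contributors to dyspnea, and a low FVC in litres cannot by itself separate restriction from short stature.

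**Working it through.** **The plan's own figure.** The only sizing of the patient–control contrast is for moderate dyspnea: 75% against 25%, 34 patients and 17 controls, α = .05, stated power 90%. The continuity-corrected two-proportion formula at 2:1 gives exactly 17 controls and 34 patients. Enumerating the continuity-corrected chi-square test gives 89.7% power. That figure stands, and this point does not affect it. The plan has no sizing for lung volumes to check.

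**Inputs.** Group sizes 34 and 17 come from the Sample Size section. The rest are assumptions, because the documents give none of them: height SD within age and sex 6 to 7 cm; slope 0.04 to 0.06 L of FVC per cm; FVC SD at given age and sex 0.6 L (variance 0.36 L²).

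**Step 1: unadjusted precision.**
- √(1/34 + 1/17) = 0.297.
- SE = 0.6 × 0.297 = 0.178 L; 95% half-width = 1.96 × 0.178 = 0.35 L.

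**Step 2: share of FVC variance due to height** = (slope × height SD)² / 0.36.
- Low: (0.04 × 6)² / 0.36 = 0.0576 / 0.36 = 16%.
- Middle: (0.05 × 7)² / 0.36 = 0.1225 / 0.36 = 34%.
- High: (0.06 × 7)² / 0.36 = 0.1764 / 0.36 = 49%.

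**Step 3: excess standard error without height** = 1 / √(1 − share).
- 16%: 1 / √0.84 = 1.09, so 9% larger.
- 34%: 1 / √0.66 = 1.23, so 23% larger.
- 49%: 1 / √0.51 = 1.40, so 40% larger.

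With height accounted for, the half-width of 0.35 L would fall to about 0.35 × √0.84 = 0.32 L at the low end and 0.35 × √0.51 = 0.25 L at the high end. The high end stacks the largest slope on the largest height SD.

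**Step 4: chance imbalance in height.**
- 1.96 × 6 × 0.297 = 3.5 cm; 1.96 × 7 × 0.297 = 4.1 cm.
- In litres: 3.5 × 0.04 = 0.14 L, up to 4.1 × 0.06 = 0.25 L.

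This is not an extra error. It is the height component of the 0.35 L half-width in step 1.

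**Step 5: what a systematic difference would do, if there were one.** A fixed height-driven shift of 0.1 L with SE 0.178 L gives a standardized shift of 0.56. The two-sided 5% test then rejects with probability Φ(0.56 − 1.96) + Φ(−0.56 − 1.96) = about 9% when there is no disease effect. A shift of 0.2 L gives about 20%. With FVC SD from 0.5 to 0.7 L, the range over both shifts is about 8% to 27%. Nothing in the documents establishes such a shift.

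**The case against.** The strongest reply is that the litre entry belongs to another analysis. Table 3 lists trial outcomes at baseline and 8 weeks, where litres are right. No sentence says that objective 1 will compare volumes in litres, and the Study Design list of what is compared with controls does not name spirometry. Scale and covariates for a secondary variable are also the kind of detail an article leaves to the full protocol or analysis plan.

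Part of this stands: litres in the patient–control comparison are inferred. But litres are the only scale given for these variables. The objective 1 model covers respiratory parameters, the heading under which the article places spirometry. And the article does name an adjustment, which is not height. Followed as written, the comparison has the weakness described.

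Four stronger readings are tempting, and the documents do not support them:

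- **That the comparison is biased by height.** No height difference between the groups is shown. The possibility is left open; it is not demonstrated.
- **That the 0.14 to 0.25 L is confounding to add to the interval.** It is chance imbalance, already inside the unadjusted confidence interval.
- **That chart height in patients against baseline-visit height in controls distorts the litre result.** A litre value contains no height. The source matters only once height is used for predicted values or adjustment.
- **That the dyspnea regression is mis-specified.** Proposed Data Analyses offers PFT parameters as possible determinants, without naming a variable or a unit.

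**Conclusion.** The point holds as a minor one. As written, the patient–control comparison of FEV1, FVC and TLC carries height variation that could be removed at almost no cost. The sure loss is precision: for FVC, a standard error about 9% to 40% too large, about 23% at the middle inputs, all resting on the assumed height SD, slope and FVC SD. No inputs were set for FEV1 or TLC, so the figures should not be carried over to them. Confounding by height is possible but not shown.

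The consequence is limited. These outcomes are secondary. Hypothesis 1 names respiratory muscle strength, peripheral airway resistance, HRQL, anxiety and depression, not lung volumes. The objective 1 sample size rests on Borg dyspnea. RV/TLC is a ratio, and the 8-week comparison in litres is sound.

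**What to change.** - In Proposed Data Analyses, state that for the objective 1 comparison FEV1, FVC and TLC are analysed as % predicted or z scores from named reference equations, or that height is a covariate in the patient–control model. Keep litres for the 8-week change.
- Wherever a lung volume is used as a determinant of dyspnea, use % predicted or z scores too. The Sample Size section allows about 10 participants per covariate, so 34 patients support about 3 determinants, and a separate height term would use one of them.
- Where still possible, take patients' height at a laboratory visit that already takes place, so that both groups have the same source. In January 2023, 8 patients had completed and 5 more were enrolled. The 5 could be measured at week 8 and the remaining 34 − 13 = 21 at baseline. The 8 would keep chart height, so the source would be mixed within the patient group, and the report should say so.

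The cost is a sentence or two of analysis wording and a brief measurement at existing visits. Height is already being collected, so the analysis change does not depend on the new measurements.

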	**PROMs^f^**					
		Dyspnea	MRC^g^ scale ratings, Borg dyspnea scale ratings, and Qualitative Dyspnea Scale ratings		Baseline (T_0_) and 8 weeks (T_2_)	
		Exercise and physical activity volume	Godin Leisure-Time Exercise Questionnaire scores		Baseline (T_0_) and 8 weeks (T_2_)	
		HRQL^h^	SF-36^i^ scores		Baseline (T_0_) and 8 weeks (T_2_)	
		Depression, anxiety, and stress	Depression, Anxiety, and Stress scale scores		Baseline (T_0_) and 8 weeks (T_2_)	
	**Cardiopulmonary exercise parameters**					
		Aerobic and anaerobic capacity	Peak aerobic capacity, anaerobic threshold, breathing reserve, and cycling power output		Baseline (T_0_) and 8 weeks (T_2_)	
		HR^j^ response and chronotropic response	HR recovery (HR at 1 minute after CPET^k^ – HR at the end of CPET) and chronotropic response index adjusted for age ([peak HR – resting HR × 100] / [220 – age] – [resting HR])		Baseline (T_0_) and 8 weeks (T_2_)	
	Neural activity during exercise (prefrontal cortex)		Oxyhemoglobin and total hemoglobin concentration changes		Baseline (T_0_) and 8 weeks (T_2_)	

^a^MIP: maximal inspiratory pressure.

^b^FEV1: forced expiratory volume in 1 second.

^c^FVC: forced vital capacity.

^d^TLC: total lung capacity.

^e^RV/TLC: residual volume/total lung capacity ratio.

^f^PROM: patient-reported outcome measure.

^g^MRC: Medical Research Council.

^h^HRQL: health-related quality of life.

^i^SF-36: Short Form-36.

^j^HR: heart rate.

^k^CPET: cardiopulmonary exercise test.

